**Methods:**

Using a concurrent pragmatic mixed methods design model we will undertake a national evaluation of CARA by triangulating quantitative data from up to nine police forces, and routine data from service providers, with qualitative data from workshop participants, victims and professional stakeholders to: (1) understand the long-term impact of CARA implementation on DVA reoffending and engagement with services and (2) explore perceptions and experiences of both delivery and receipt of CARA. We will use qualitative methodologies that draw on interpretivist and phenomenological perspectives, as well as quantitative methodologies using interrupted time series models, Poisson regression models, Geo mapping and a cost benefits analysis.

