## Introduction

Domestic violence and abuse (DVA) is a grave human rights violation and represents a global public health epidemic (
Alhabib *et al.*, 2010; Ellesberg & Heise, 2005;
Joachim, 2000), resulting in increased use of health services and vast social and economic costs (
Oliver *et al*., 2019). DVA is associated with a range of negative health and social outcomes including chronic pain, physical disability, poorer reproductive health, acquisition of HIV or other STIs, substance misuse and can also lead to death (
WHO, 2013). DVA is also linked to the exacerbation of mental health issues including PTSD symptoms, anxiety, and depression (
Ferrari *et al.*, 2014). There is now a strong body of empirical evidence demonstrating that, across a wide range of settings, women and girls are at more risk of violence perpetrated by an intimate partner than anyone else (
Oram *et al.*, 2022). Thus, whilst women are not the sole victim-survivors of DVA nor is it exclusive to heterosexual intimate relationships, they do represent the majority of victim-survivors worldwide. Current prevalence data suggests that over 2 million incidents relating to DVA in England and Wales occurred over a one-year period leading up to March 2023, with under half recorded as criminal offences (
ONS, 2023). These figures are likely to be a significant underestimate due to limitations of data capture methods. It is challenging to accurately reflect and measure the true prevalence of domestic violence given the secrecy and stigma which continues to surround it.

Measures and interventions that aim to reduce prevalence and/or the harms associated with DVA have gained traction over the last few decades, including the adoption of a public health approach similar to the approach taken to the management of physical violence within cities (
Chandan *et al*., 2020). However, there has also been a sustained reduction in capacity across the criminal justice system (CJS) at a time of increasing demand (
McConville & Marsh, 2020). Stakeholder consultation suggests that the CJS is struggling to constructively support victim-survivors, deter offenders or reduce reoffending, by means of an early intervention. Victim-survivors report feeling a lack of justice in formal systems dealing with DVA (

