### Analysis of quantitative data

**
*Interrupted time series*
**. Using interrupted time series (ITS), we will also examine whether the introduction of the CARA conditional caution leads to a hypothesised population-based reduction in the incidence of DVA, as hypothesised in Figure 2. A secondary outcome will be to assess if there was a change in the severity of recorded DVA before and after the introduction of CARA.

 As an intervention study design, ITS is a valuable study design compared to traditional observational study designs (such as cohort or case control studies) particularly when there is a need for retrospective evaluations which have already been implemented, either without randomization or to a whole population, both of which are applicable in the CARA intervention (
Bernal *et al.*, 2017). By nature, ITS can be applied to natural experiments when an intervention is introduced at the population level at a clearly defined period of time and involves observing a single population over time.

In an ITS study, a time series of the outcome of interest (incidence of domestic violence and abuse) is used to establish an underlying trend, which is ‘interrupted’ by an intervention (e.g. CARA being offered in a force area) at a known point in time. The pre-intervention underlying trend is compared with the post-intervention period to identify whether the intervention is associated with any changes in outcome.

Initially summary statistics and plots will be undertaken, including a scatter plot of the time series demonstrating before and after comparisons of the incidence of DVA across the force areas. These will include sub-analyses, by age, gender, ethnicity, force area and whether in same sex relationship.

Following this a segmented regression model such as the one below will be constructed to undertake the ITS model:

Yt-=α+β1Tt+β2Xt+β3XtTt

Yt is the aggregated outcome variable measured at each equally-spaced time point (month)

Tt is time

Xt is study phase

XtTt is time after interruption

α, β1, β2 and β3 are model parameters

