As our outcome measure (DVA occurrences) are count data, we will also undertake a Poisson model. Calendar quarters will be included as a categorical variable to account for seasonality. The final model will provide a measure of relative risk with 95% confidence intervals to describe the change in incidence in DVA across the CARA sites before and after the introduction of the intervention. We will account for covariates of interest in the final model to examine any changes specific to offender subgroups of interest, including age, sex, ethnicity and socioeconomic status. Confounding events or co-interventions that will affect study outcome will be explored through consultation with the research team, including all stakeholders, and through the qualitative research. Time varying confounders might include, for example, lockdowns from the COVID-19 pandemic.

Where possible we will also aim to undertake a controlled interrupted time series (CITS) (
Bernal *et al.*, 2018). In this case the control data will be derived from sites where CARA was not delivered during the study timeframe. The CITS model can be described as:

Yt-=α+β1Tt+β2Xt+β3XtTt+β4Zt+β5ZtTt+β6ZtXt+β7ZtXtTt

Yt is the aggregated outcome variable measured at each equally-spaced time point (month)

Tt is time

Xt is study phase

XtTt is time after interruption

Zt is treatment or control group

ZtTt is time for treatment and 0 for control,

ZtXt is study phase for treatment and 0 for control,

ZtXtTt is time after interruption for treatment and 0 for control

α, β1, β2 , β3 β4, β5, β6 and β7 are model parameters

**
*Geomapping*
**. We will also undertake geomapping using postcode data from regional and national data (either from the address where the incident took place or the perpetrator’s address). The postcode data will be input using googlemaps to generate a visual-coloured map. The visuals produced through this method are not accurate enough to render an individual’s home address to become identifiable; postcodes are replaced with colour patches, similar to heat maps, covering a large area. The postcodes entered into google through this process are not stored by google and therefore no data will be stored and shared through this method.

**
*Health economics analysis*

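### The interrupted time series names a Poisson model with no stated allowance for overdispersion or serial correlation, so its intervals could be materially too narrow, and covariate adjustment cannot show the promised subgroup changes

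*Protocol article*

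**What the plan says.** Under Analysis of quantitative data (Interrupted time series), the protocol article gives a segmented regression of a monthly aggregate on time, study phase and time after interruption. It then turns to the type of outcome: "As our outcome measure (DVA occurrences) are count data, we will also undertake a Poisson model". Seasonality is handled as follows: "Calendar quarters will be included as a categorical variable to account for seasonality". The reported quantity is fixed: "The final model will provide a measure of relative risk with 95% confidence intervals". Its stated purpose is to describe how incidence changed across the CARA sites. A controlled version with four further terms is planned where possible.

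On subgroups the same paragraph says: "We will account for covariates of interest in the final model to examine any changes specific to offender subgroups of interest", and lists age, sex, ethnicity and socioeconomic status.

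Neither printed equation has an error term. The text does not mention dispersion, robust standard errors or correlation between months. It gives no monthly count for any series. The only volume figure is in the Introduction: "over 2 million incidents relating to DVA in England and Wales occurred over a one-year period leading up to March 2023". Fewer than half of these, it adds, were entered as crimes.

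**The concern.** A Poisson likelihood sets the variance equal to the mean. That an outcome is a count does not make this true. Recorded domestic abuse can move from month to month for reasons outside trend and quarter, and the article itself names lockdowns as a time-varying influence. Neighbouring months may also be correlated. Model-based Poisson errors ignore both. The larger the monthly count, the smaller the Poisson standard error becomes relative to the real month-to-month variation.

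The time series answers the objective on population-level incidence and severity, and the results are meant for government departments. An interval that is too narrow could present ordinary fluctuation as a CARA effect, in either direction.

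The subgroup sentence raises a separate problem. Adding age, sex, ethnicity or socioeconomic status as covariates gives one CARA effect, assumed common to all groups. It does not estimate whether the change differs between groups. The section on population, intervention, comparison and outcome gives subgroup insight as a reason for a national study.

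**Working it through.** The article states no dispersion, power or interval width, so there is no figure of its own to reproduce. The check asks what happens if the named model is fitted with model-based errors.

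**Volume**
- From the Introduction: 2,000,000 / 12 = about 167,000 incidents a month nationally.
- Assumed, not in the document: 43 forces of equal size. 167,000 / 43 = about 3,900 incidents per force-month. With under half recorded as crimes, this is below about 1,940 crimes; 1,900 is used.
- The abstract speaks of "triangulating quantitative data from up to nine police forces". Nine equal forces pooled give 9 × 3,876 = about 35,000 a month.

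**Formulas**
- Let μ be the monthly mean and CV the residual variation beyond Poisson, trend and season (assumed).
- Dispersion φ = 1 + μ × CV².
- Standard errors are too small by a factor √φ.
- Actual two-sided error of a nominal 5% test, independent months: 2 × [1 − Φ(1.96/√φ)].
- Example: μ = 3,900, CV = 3%: φ = 1 + 3,900 × 0.0009 = 4.51; √φ = 2.12; error = 36%.

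| μ per month | CV | φ | √φ | False-positive rate |
|---|---|---|---|---|
| 50 | 3% | 1.04 | 1.02 | 5.5% |
| 200 | 3% | 1.18 | 1.09 | 7% |
| 200 | 5% | 1.50 | 1.22 | 11% |
| 200 | 10% | 3.00 | 1.73 | 26% |
| 1,900 | 3% | 2.71 | 1.65 | 23% |
| 1,900 | 5% | 5.75 | 2.40 | 41% |
| 3,900 | 1% | 1.39 | 1.18 | 10% |
| 3,900 | 3% | 4.51 | 2.12 | 36% |
| 3,900 | 5% | 10.75 | 3.28 | 55% |
| 35,000 | 1% | 4.50 | 2.12 | 36% |
| 35,000 | 3% | 32.50 | 5.70 | 73% |

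**Simulation check**

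The segmented Poisson model with quarter terms was fitted to series with no true effect, and the level change was tested. Assumed: 72 months, interruption at month 36, lag-1 autocorrelation 0 or 0.4, 600 runs per setting (Monte Carlo error at most about 2 percentage points).

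| μ | CV | Unscaled, ρ = 0 | Unscaled, ρ = 0.4 | Dispersion-scaled, ρ = 0 | Dispersion-scaled, ρ = 0.4 |
|---|---|---|---|---|---|
| 1,900 | 3% | 22.5% | 35% | 5% | 14% |
| 1,900 | 5% | 42% | 56% | 5% | 17% |
| 3,900 | 3% | 40% | 52.5% | 5% | 15.5% |
| 3,900 | 5% | 57% | 66% | 6% | 18% |

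- With essentially no extra variation, the unscaled test stays close to 5% (4 to 6%) at every volume. Large counts amplify the problem; they do not cause it.
- At ρ = 0.4, dispersion scaling alone leaves 14 to 24% false positives for means of 1,900 or more and CV of 3 to 10%. A second set-up (36 months before, 24 after, CV 3 to 8%) leaves 12 to 21%.
- In that second set-up, at μ = 3,876, CV 5% and ρ = 0.4, the true standard error was 0.040 against a model value of 0.0089, a ratio of 4.5.

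**Subgroups**

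In a log-linear model, a main effect for subgroup shifts that group's baseline and leaves β2 and β3 common to all groups. A subgroup-specific change is the product of subgroup with Xt and with time after interruption. The article describes no such term. Its planned sub-analyses by age, gender, ethnicity, force area and same-sex relationship belong to the initial summaries and plots.

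**The case against.** The strongest case against is that this reads silence as error. The article does not say that the Poisson errors are unscaled or that months are treated as independent. Quasi-Poisson and Newey-West errors keep the Poisson mean model, so the wording does not exclude them, and such detail is often left to an analysis plan. The article does not literally call the Poisson model the final one either, although a relative risk points to a log-linear count model. All this stands. A reader might infer that the plan prescribes an unscaled fit and that its intervals will be several times too narrow. The document supports neither statement: it gives no series counts, residual variation or autocorrelation, and the division by 43 forces is an assumption.

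It can also be said that counts may be small, because the quantitative population is defined as those eligible for CARA. That definition follows the introduction to the matched-cohort details. The time series concerns population-level occurrences across sites, so force-level volumes are the more natural reading. The subgroup series could still be small, and there the inflation is modest.

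The primary outcome, reoffending within 12 months, is set out with the matched cohort, so the time series is not the only route to a conclusion. The controlled design may remove shocks shared with control areas, but it does not by itself correct the standard errors.

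On subgroups, the wording is loose and does not forbid interactions. As it stands, however, it names covariate adjustment as the means to an end that adjustment cannot reach.

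**Conclusion.** The point holds in conditional form. The article chooses Poisson because the outcome is a count, promises 95% intervals, and states no allowance for overdispersion or serial correlation. If model-based errors are used on force-level or pooled counts, the intervals could be materially too narrow: about 1.7 to 3.3 times at 1,900 to 3,900 events per month with 3 to 5% residual variation, with false positives of 23 to 55% against 5%. Autocorrelation raises this further. At 50 to 200 events per month and the same variation, the factor is only 1.02 to 1.22. If there is no extra variation, there is no understatement.

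These sizes rest on assumed force volumes, residual variation, series length and autocorrelation. They show what the named model is exposed to and do not predict this study's error rate.

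The subgroup point needs none of these assumptions. Covariate adjustment gives one common effect and cannot show subgroup-specific change. The quarterly seasonal terms and the lack of a stated population offset are not errors.

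**What to change.** State that the count models for both the simple and the controlled interrupted time series will be quasi-Poisson or negative binomial, with autocorrelation-robust (for example Newey-West) or AR(1) errors. Both parts are needed, because dispersion scaling alone left about 12 to 24% false positives at lag-1 autocorrelation 0.4 for force-level or larger counts. Newey-West and AR(1) errors were not simulated here, and Newey-West can under-correct in short series. The text should therefore name the lag choice and a check of residual autocorrelation.

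Replace covariate adjustment for subgroup changes with interactions of subgroup with Xt and with time after interruption, fitted to subgroup-specific monthly counts.

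The cost is mainly wording, plus wider intervals. Because police data arrive aggregated, the extraction must supply monthly counts by subgroup. This includes socioeconomic status, which is absent from the list of planned descriptive sub-analyses. A population offset and monthly or harmonic seasonal terms are optional refinements.

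### Calendar-quarter terms are too coarse for a monthly count series: month length and within-quarter season can shift the uncontrolled step estimate by a few per cent, depending on start month (minor)

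*Protocol article*

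**What the plan says.** All of this stands in the protocol article, Analysis of quantitative data, under Interrupted time series.

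- Time unit: "Yt is the aggregated outcome variable measured at each equally-spaced time point (month").
- Model form, given as an example: "Following this a segmented regression model such as the one below will be constructed to undertake the ITS model". It has a level, a trend, a step and a slope change.
- Count model: "As our outcome measure (DVA occurrences) are count data, we will also undertake a Poisson model".
- Season: "Calendar quarters will be included as a categorical variable to account for seasonality".
- Result: "The final model will provide a measure of relative risk with 95% confidence intervals to describe the change in incidence in DVA".
- Control series, conditional: "Where possible we will also aim to undertake a controlled interrupted time series (CITS").

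The interruption is the date on which a force begins to offer CARA. The article gives no start months, series length, monthly counts, offset or standard-error method.

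**The concern.** The seasonal term is coarser than the time unit. Months are treated as equal steps, but they run from 28 to 31 days, so a constant daily rate still gives an uneven monthly count. Quarter terms remove differences between quarters and leave those within a quarter. What is left is a fixed calendar pattern, not random noise.

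Two things could follow. First, if CARA starts in the middle of a quarter, the segments before and after begin and end at unbalanced points of that pattern, and the step term absorbs part of it. Second, a plain Poisson model takes its variance from the mean alone and makes no allowance for the leftover pattern. A force-level estimate could then carry a small artefact whose direction depends only on the start month.

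**Working it through.** The article states no power, error rate or expected effect for this analysis, so there is no figure to reproduce. The check asks what the stated model returns when CARA has no effect.

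**Inputs.** From the article: monthly counts, Poisson model, trend, step, slope change, three quarter dummies, no offset mentioned. Calendar fact: month lengths. Assumed, because not given: 24+24 months (also 36+24 and 60+36); a start in each of the twelve months; 50 to 3,000 events a month; a season of either +6% in December and +7% in July, or a smooth annual cycle of 5% or 10% amplitude.

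**Step 1: what quarter terms leave behind.** In an ordinary year the first quarter averages (31 + 28 + 31)/3 = 30 days. January and March therefore sit 1/30 = 3.3% above the quarter mean and February 2/30 = 6.7% below it. In the other quarters the mean is 30.33 or 30.67 days and the deviations are about 1.1% and 2.2%. The mean squared deviation is 0.00222 in the first quarter and about 0.00024 in each of the others, so (0.00222 + 3 × 0.00024)/4 ≈ 0.00073 overall.

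**Step 2: how visible this is.** For a mean monthly count N, the Pearson dispersion is roughly 1 + 0.00073 × N:

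- N = 50: 1 + 0.04 = 1.04
- N = 200: 1 + 0.15 = 1.15
- N = 2,000: 1 + 1.46 = 2.46 (simulation gave 2.5)

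The leftover pattern is lost in count noise at 50 a month and dominates it at 2,000.

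**Step 3: bias of the step.** The model was fitted to the exact expected counts, with true rate ratio 1. The range is over start months.

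| Series | Month length only | Plus 10% cycle |
|---|---|---|
| 24+24 | 0.986 to 1.018 | 0.971 to 1.039 |
| 36+24 | 0.989 to 1.018 | 0.977 to 1.031 |
| 60+36 | 0.993 to 1.012 | 0.987 to 1.020 |

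Where the leap year falls changes the limits a little; other placements at 24+24 gave 0.986 to 1.015 and 0.984 to 1.022 for month length alone. With the December and July peaks, 24+24 months gave 0.966 to 1.027. Starts in January, April, July or October gave only about 1.001 to 1.006. The log step averaged over all twelve start months gave a rate ratio of about 1.000 to 1.003. In a controlled series with the same calendar, start and season in both groups, the difference in steps was 1.000.

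**Step 4: false positives at a nominal 5%.** 24+24 months, 12 start months × 150 runs = 1,800 series per cell. The simulation error near 5% is √(0.05 × 0.95/1,800) ≈ 0.5 percentage points.

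| Assumed count per month | Month length only | Plus December and July peaks |
|---|---|---|
| 50 | 5.3% | 5.6% |
| 200 | 6.7% | 6.9% |
| 500 | 6.7% | 8.5% |
| 2,000 | 11.4% | 21.3% |
| 2,000, dispersion-scaled errors | 1.3% | 0.9% |

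Repeat runs at 200 a month fell between 5% and 8%. Single start months can be worse: at 1,000 a month and 36+24 months, month length alone gave about 17% to 20% in the least favourable one. Newey-West errors rejected about 10% to 11% of the time even with the corrected seasonal terms, so that average excess is not due to the quarters. With quarters, their worst start months reached 19% to 28% at 1,000 to 3,000 a month.

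**Step 5: the corrected model.** Month dummies with a log(days) offset gave a step of 1.000 for every start month and an average plain-Poisson false-positive rate of 4.4% to 5.5%. Quarter terms with the offset cure only the month-length part: with a 10% cycle at 36+24 months the range was still 0.980 to 1.021. Two harmonic pairs with the offset gave 1.000 for a smooth cycle, but 0.987 to 1.014 remained with the December and July peaks.

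**The case against.** The strongest reply is that the effect is small and often disappears. That largely stands. Month length gives 1% to 2%, and the larger figures rest on assumed seasons. The result is described across the CARA sites, where varied start months would offset one another. The planned controlled analysis can remove the shift entirely. Two limits remain: the control is planned only where possible, and summaries by force area are also planned, where one start month applies and nothing averages out.

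The second reply concerns counts. The Introduction cites "over 2 million incidents relating to DVA in England and Wales occurred over a one-year period leading up to March 2023", which is about 2,000,000/12 ≈ 167,000 a month; a series holding 1% of that would have about 1,670. The Population paragraph, however, restricts the sample to those eligible for CARA. If that applies to the time series too, counts could be far lower and the false-positive problem slight or absent.

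Third, the segmented model is offered as an example, and an article may leave offsets and variance estimators to the full plan. Their absence here is therefore not a fault. The quarter term is different: it is stated.

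A reader might also infer more than the article supports:

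- That false positives are inflated in general. This needs high counts and unscaled errors, neither of which the article states; with dispersion scaling the average goes the other way.
- That the shift rivals the expected population effect. The article gives no expected effect to compare it with.
- That the authors weighed monthly terms and rejected them. Nothing in the text says so.

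**Conclusion.** The mismatch between a monthly series and a quarterly seasonal term is certain from the text. Its consequence is modest. In a single uncontrolled series the step rate ratio is shifted by up to about 1% to 2% from month length and about 3% to 4% under the assumed seasons, in a direction set by the start month. Quarter-boundary starts, pooling over varied starts, or a control sharing calendar, start and season bring it close to zero.

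As between unscaled and dispersion-scaled Poisson errors, the interval is too narrow only with unscaled errors and high counts: the average false-positive rate is about 5% at 50 a month, 5% to 8% at 200 and 11% to 21% at 2,000. Scaled errors make the interval on average too wide, which costs precision and leaves the shift in place. Counts, series lengths, start months and seasonal shapes are assumptions; month lengths are not. Severity: minor.

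**What to change.** Replace the calendar-quarter factor with month-of-year effects (11 dummies) and add log(days in month) as an offset, in both the single and the controlled series. For short series, use harmonic pairs with the same offset, and state that these follow a smooth season but not single-month peaks.

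The cost is 11 − 3 = 8 more parameters, taking the single-series model from 7 to 15 in a series of, say, 48 points. Two harmonic pairs need 4 − 3 = 1 more. No new data are required, since month length comes from the calendar.

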### Population, intervention, comparison and outcome

A previously published study examining the impact of the CARA was undertaken across the West Midlands (
University of Birmingham, 2021). As part of that project a PSM cohort approach was chosen to disentangle the treatment effects from confounding variables which may exist in this study (
Figure 1). However, as this study was only undertaken in one locality it was not sufficiently powered nor contained a diverse enough population to examine whether changes in recidivism or reoffending differed per offender sub-groups in the population such as by age, sex, ethnicity or socio-economic group. Undertaking such an evaluation of these sub-groups would be invaluable in providing further insight into specific groups of offenders who may respond better or worse to the CARA intervention. In this study, we will be able to do this as we are undertaking a nation-wide study to examine the effects of the interventions. Further details on the PSM cohort approach are below:

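### Subgroup-specific change in the interrupted time series is to be examined by covariate adjustment, which by itself gives one common relative risk and cannot show whether the change after CARA differs between subgroups

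*Protocol article*

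**What the plan says.** The protocol article, under Analysis of quantitative data, sets out a segmented regression for the monthly aggregated outcome, offered as an example of the model to be built: "Yt-=α+β1Tt+β2Xt+β3XtTt". The terms are time, study phase and time after interruption. A Poisson version with calendar quarter as a categorical variable follows. Its output is described thus: "The final model will provide a measure of relative risk with 95% confidence intervals", for the change across the CARA sites.

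The next sentence deals with subgroups: "We will account for covariates of interest in the final model to examine any changes specific to offender subgroups of interest". It names age, sex, ethnicity and socioeconomic status.

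Where possible, a controlled series will be fitted as well: "Yt-=α+β1Tt+β2Xt+β3XtTt+β4Zt+β5ZtTt+β6ZtXt+β7ZtXtTt". Here Z marks treatment or control.

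The only other subgroup step for the time series belongs to the initial summary statistics and plots: "These will include sub-analyses, by age, gender, ethnicity, force area and whether in same sex relationship". Socioeconomic status is not on that list.

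Separately, the section Population, intervention, comparison and outcome introduces the propensity-score-matched cohort. It says of the earlier one-locality study that, for subgroup questions, "it was not sufficiently powered nor contained a diverse enough population", and continues: "In this study, we will be able to do this as we are undertaking a nation-wide study to examine the effects of the interventions".

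**The concern.** The sentence on subgroups joins a purpose to a method, and the method does not serve the purpose. Accounting for a covariate answers whether the overall change persists once the mix of offenders is allowed for. A change specific to a subgroup is a different question: does the effect of phase itself vary with the covariate? That needs product terms between subgroup and phase, or separate series that are then formally compared. The article names neither for the inferential model.

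An analyst who follows the sentence as written would report one relative risk, adjusted for age, sex, ethnicity and socioeconomic status. If the change differs between groups, and above all if it runs in opposite directions, that single figure describes neither group. The findings are meant for the Home Office and the Ministry of Justice, and an adjusted average could be taken as showing that all offender groups respond alike.

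**Working it through.** The article gives no sample size, event rate, effect size or subgroup share for the quantitative study, so there is no planned figure to reproduce. All relative risks, shares and series lengths below are assumptions for illustration.

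**Step 1. Which terms the article provides.**

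| Element | Terms with a subgroup | What it yields |
|---|---|---|
| Time series equation | none | step and slope change for the whole series |
| Controlled series equation | none; interactions involve only Z, time and phase | CARA versus control difference in step and slope |
| Sentence on covariates | subgroup variables accounted for | level adjustment, if read literally |
| Initial plots and summaries | breakdown by five variables, without socioeconomic status | description without a tested contrast |

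**Step 2. What adjustment does.** Let g = 0 or 1 mark the subgroup. With the covariate as a main effect,

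log μ = α + β1·T + β2·X + β3·X·T + γ·g.

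Within subgroup g, the ratio of the expected count after the interruption to the count projected from the earlier trend is exp(β2 + β3·time after interruption). The term γ·g cancels, so the ratio is the same for g = 0 and g = 1 whatever the data show.

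**Step 3. Which value it returns.** Take a flat baseline and a pure step change, with p the pre-interruption share of the second subgroup. The Poisson fit matches the total count in each phase, so

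common RR = (1 − p)·RR₁ + p·RR₂.

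- RR₁ = 0.85, RR₂ = 1.10, p = 0.25: 0.75 × 0.85 + 0.25 × 1.10 = 0.6375 + 0.275 = 0.9125, about 0.91.

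The quantity of interest here is the ratio of relative risks, 1.10 / 0.85 = 1.29. The adjusted model has no parameter for it.

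**Step 4. Check by fitting.** A segmented Poisson regression was fitted to noise-free expected counts (24 months before, 24 after) with true values 0.80 and 1.10.

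| Share of second subgroup | RR, subgroup as main effect only | RRs with subgroup-by-phase term |
|---|---|---|
| 10% | 0.83 | 0.80 and 1.10 |
| 20% | 0.86 | 0.80 and 1.10 |
| 50% | 0.95 | 0.80 and 1.10 |

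The formula in step 3 gives the same three values (for example 0.8 × 0.80 + 0.2 × 1.10 = 0.86). One added product term recovers both subgroup effects.

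**Step 5. The separate statement on the matched cohort.** Against the same subgroup contrast in one force, nine equal forces reduce the standard error by √9 = 3 at every subgroup share, so going multi-force does help. Whether it helps enough depends on the share f. Suppose one force alone had 80% power for the overall effect (two-sided 5%) and the interaction is as large as that effect. Then power with nine forces is Φ(2.80·√(9·f·(1 − f)) − 1.96):

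| f | 50% | 20% | 10% | 5% |
|---|---|---|---|---|
| Power | 99% | 92% | 71% | 45% |

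The article gives neither the subgroup shares nor one force's precision, so it cannot be said from the document where the planned subgroups fall.

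**The case against.** The best defence is that the sentence states an aim of effect modification and does not fix a main-effects model. The segmented regression is offered as an example. The printed equations are schematic: they omit even the calendar quarters that the text says will be included, so the absence of a subgroup product term in them proves little. A relative risk could be reported for each subgroup, and an article commonly leaves exact interaction terms to an analysis plan.

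Much of this stands. The article does not rule out interactions, and the equations alone would not make a finding. What remains is that the article is not silent here. It names a method for subgroup change, and that method is covariate adjustment. The promised breakdowns do not close the gap, because they are descriptive and leave out socioeconomic status.

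A reader might infer two stronger claims that the document does not support.

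- *That aggregated data allow subgroup variables to enter only as monthly proportions.* Aggregated counts can be held as month-by-subgroup cells, and the planned breakdowns already imply such cells for most of the variables.
- *That the study's stated purpose of learning who responds better or worse goes untested, or that its claim about a nation-wide sample is wrong.* That purpose and claim are set out for the matched cohort, whose outcome model the article does not print. A loose sentence about the time series says nothing on what the cohort will test. A multi-force sample also does raise subgroup precision, as step 5 shows.

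**Conclusion.** The point holds for the time series. Read literally, the stated method returns one common relative risk and cannot show a difference in change between subgroups. That result is structural and does not depend on the assumed numbers. The size of the distortion does: about 0.91 in place of 0.85 and 1.10 in the example, and 0.83 to 0.95 in place of 0.80 and 1.10 across shares of 10% to 50%. These figures assume a step change on a flat baseline. If the analysts already intend interaction terms, the defect is one of wording and is settled by stating them.

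The assurance for the matched cohort is a minor, separate matter. It is plausible for large subgroups, but no figure in the article shows that the sample suffices for small ones. It should not be read as evidence that subgroup analysis will fail.

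**What to change.** In the interrupted time series text under Analysis of quantitative data, replace the sentence on covariates with a stated effect-modification analysis:

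- Obtain monthly counts split by each subgroup variable, including socioeconomic status. The variables can be taken one at a time and need not be cross-classified.
- For each variable, add subgroup-by-phase and subgroup-by-time-after-interruption terms to the Poisson model, together with the subgroup and subgroup-by-time terms they require. In the controlled series, add the interaction of these terms with Z.
- Report the relative risk in each subgroup and the ratio of relative risks with its 95% interval.
- If covariate adjustment of the overall effect is also wanted, state it separately as adjustment.

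The cost is a finer extract from each force, which should be checked against the information sharing agreements already signed, and wide intervals for small subgroups. No new data collection is needed. For the matched cohort, a sentence giving the expected subgroup numbers, once known, would support the assurance made there.
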